**Criteria for termination of the study**	
1	An unintended, significant or unacceptable risk to the subject is identified
2	A significant failure of the protocol is discovered during trial execution
3	The investigational drug/trial treatment is ineffective, or it is not meaningful to continue the trial
4	Extreme difficulty in completing the trial due to serious delays in subject enrollment or frequent protocol deviations

### Intervention

Eligible patients will receive oral fluzopalib150mg twice daily and oral anlotinib 8 mg once daily until disease progression or development of intolerable toxic side effects. The dose giving and dose level adjustment are shown in Table 2.

**Table 2 Tab2:** Dose adjustment criteria

NCI CTCAE 5.0		Management (after active treatment and observation)	Dose adjustment after the study drug is continued
**Anlotinib**			
**Abnormal liver function**	**Grade 1**	**Conduct follow-up as planned**	**8 mg****, ****qd**
	**Grade 2 (normal baseline)**	**Delay dose, strengthen guarantees the liver treatment and close monitoring of liver function once a week till < grade 2 within 2 weeks, and then continue anlotinib at a lower dose level**	**8 mg****, ****qod**
	**Grade 2 (abnormal baseline)**	**Strengthen guarantees the liver treatment and close monitoring of liver function once a week, continue anlotinib at an o initial dose**	**8 mg****, ****qd**
	**Grade 3**	**Delay dose, strengthen guarantees the liver treatment and close monitoring of liver function twice a week till < grade 2 within 2 weeks, till < grade 2 within 2 weeks, and then continue anlotinib at a lower dose level**	**8 mg****, ****qod**
	**Grade 4**	**Strengthen guarantees the liver treatment and close monitoring of liver function once/twice a week till < grade 2. Or have reasons for this issue**	**Discontinue anlotinib**
**Hypertension**	**SBP 120–139 mmHg or DBP 80–89 mmHg**	**Closely monitor, continue anlotinib at an initial dose**	**8 mg****, ****qd**
	**Asymptomatic grade 2 hypertension**	**Continue anlotinib at an initial dose. Start taking antihypertension medication or adjust its dose till blood pressure is effectively controlled (SBP < 140 mmHg or DBP < 90 mmHg) within two weeks, otherwise dose can be reduced as per investigator’s discretion**	**8 mg****, ****qd, or dose can be reduced as per investigator’s discretion**
	**Symptomatic grade 2 hypertension, or grade 3 hypertension**	**Discontinue anlotinib, and then start taking antihypertension medication or adjust its dose till blood pressure is effectively controlled within two weeks, continued anlotinib at an initial dose or a lower dose level**	**8 mg****, ****qd, or 8 mg****, ****qod as per investigator’s discretion**
**Abnormalities of bleeding and coagulation**	**Grade 1**	**Closely monitor, continue anlotinib at an initial dose**	**8 mg****, ****qd**
	**Grade 2**	**Discontinue anlotinib, till AE ≤ 1, and then continue anlotinib at a lower dose**	**8 mg****, ****qod**
	** ≥ Grade 3, or ≥ Grade 2 occurred twice (after discontinue or dose adjustment)**		**Withdraw from the pilot study**

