Anlotinib is also a pan-inhibitor of VEGFR, which also inhibits *PDGFR*, *FGFR*, c-*KIT* and other targets, and would have synergistic antitumor effect in combination with the PARP inhibitor fluzoparib theoretically. However, till now no clinical study on the combination of anlotinib and fluzoparib have been reported or registered. Pharmacokinetically, anlotinib is not the substrates of P-glycoprotein, mainly metabolized via CYP1A2 and CYP3A4/5, and mostly excreted in urine and feces. In terms of drug interactions, anlotinib has a moderate inhibitory effect on CYP3A, CYP2B6, CYP2C8, CYP2C9 and CYP2C19. Grade 3 or higher adverse reactions are mainly hypertension, hand-foot skin reaction and proteinuria. Fluzoparib is a substrate of the efflux transporter P-glycoprotein mainly metabolized via CYP3A4, and is mostly excreted as metabolites in urine and feces. In terms of drug interactions, fluzoparib has a relatively small effect on the inhibition of each CYP enzyme subtype and does not induce CYP3A4 or CYP1A2. The most common grade ≥ 3 treatment-emergent adverse events reported in the fuzuloparib group were anemia (25.1%), decreased platelet count (16.8%), and decreased neutrophil count (12.6%) [12]. The above pharmacokinetic studies showed metabolic transformation is the main pathway of anlotinib elimination, while renal excretion via urine was the main excretion route and fecal excretion was the secondary excretion route of fuzuloparib, therefore, the toxicity of the two drugs should not add up theoretically. In addition, real-world study data for a small number of patients treated with fluzoparib in combination with anrotinib showed no significant increase in toxic and side effects.

The combination of anlotinib and fluzoparib may theoretically decrease the metabolism of fluzoparib, increase its concentration in the blood and area in the drug curve. Therefore, fluzoparib dose should be reduced appropriately. Combination of anlotinib and fluzoparib would not make adverse events and not increase the incidence of ≥ grade 3 adverse events. In theory, it is feasible in combination of the anlotinib and fluzoparib.

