6	Have received chemotherapy, radiotherapy or other experimental anticancer therapy (other than bisphosphonates) within 4 weeks prior to the first dose: those who have received prior local radiotherapy may be enrolled if the following conditions are met: the radiotherapy ended more than 4 weeks (more than 2 weeks for brain radiotherapy) from the start of study treatment; and the target lesion selected for this study is not in the radiotherapy area; or the target lesion is in the radiotherapy area but has been confirmed progression.
7	Patients who have not recovered from antineoplastic therapy-related adverse effects (except alopecia) to NCI-CTCAE ≤ grade 1 after prior systemic antineoplastic therapy.
8	Abnormal coagulation (INR > 1.5 or prothrombin time (PT) > ULN + 4 s or APTT > 1.5 ULN), with prone to bleeding or on thrombolytic or anticoagulant therapy; Note: The use of low-dose heparin for prophylactic purposes (adult daily dose of 0.6 to 1.2 10,000 U) or low-dose aspirin (dosage ≤ 100 mg daily) is accepted for prophylactic purposes.
9	Clinically significant hemoptysis (hemoptysis > ½ tablespoon per day) within 3 months prior to enrollment; or clinically significant hemorrhage symptom or prone to bleeding within 4 weeks prior to cohort, such as alimentary tract hemorrhage, hemorrhagic gastric ulcer (including gastrointestinal perforation and/or fistula, but the gastrointestinal perforation or fistula that has been surgically removed may be allowed), fecal occult blood (≥ + +) at baseline, unhealed wounds, ulcers, or fractures.
10	Renal insufficiency: urine protein ≥ + + , or 24-h urine protein amount > 1.0 g.
11	Patients with poor blood pressure control (systolic blood pressure ≥ 160 mmHg and diastolic blood pressure ≥ 100 mmHg) after drug therapy.
12	Patients with severe cardiovascular disease: grade II or higher myocardial ischemia or myocardial infarction, poorly controlled arrhythmias; grade III-IV cardiac insufficiency by NYHA criteria, or cardiac ultrasound suggestive of left ventricular ejection fraction (LVEF) < 50%.
13	The current presence of peripheral neuropathy ≥ CTCAE degree 2, except the cause of trauma.

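### Table 2 counts blood pressure as controlled when only one of the two pressures is below its limit (SBP < 140 or DBP < 90); it should require both

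*Protocol article*

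**What the plan says.** The Intervention section refers to Table 2 for dose adjustment, and Table 2 is keyed to NCI CTCAE 5.0. Its anlotinib part has three hypertension rows.

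- **First row**, "SBP 120–139 mmHg or DBP 80–89 mmHg": close monitoring, anlotinib unchanged at 8 mg once daily.
- **Asymptomatic grade 2**: anlotinib continues at the initial dose, and antihypertensives are started or adjusted "till blood pressure is effectively controlled (SBP < 140 mmHg or DBP < 90 mmHg) within two weeks". If that is not reached, "otherwise dose can be reduced as per investigator’s discretion".
- **Symptomatic grade 2, or grade 3**: anlotinib is stopped and antihypertensives are given "till blood pressure is effectively controlled within two weeks, continued anlotinib at an initial dose or a lower dose level". This row uses the same term but attaches no numbers to it.

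The asymptomatic grade 2 row is the only place in the article that says in figures what on-treatment control means. Nothing elsewhere says that both limits must be met.

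**The concern.** An elevation is properly described with *or*, since either raised pressure is enough to make it one. Control is the opposite state, so both pressures must be below their limits, and that calls for *and*. The table uses *or* for both.

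The definition does two jobs in its row. First, it is the end point of antihypertensive treatment: "Start taking antihypertension medication or adjust its dose till blood pressure is effectively controlled". Read literally, adjustment may stop while one pressure is still raised. Second, it sets the two-week failure condition after which a dose reduction may be considered, and a patient with only one raised pressure does not meet that condition.

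This is a safety rule for a known toxicity. The Background says of anlotinib: "Grade 3 or higher adverse reactions are mainly hypertension, hand-foot skin reaction and proteinuria". In a multi-center study a printed threshold should mean the same at every site without anyone correcting it silently.

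**Working it through.** The check is one of logic; it uses no error rate, power or sample size.

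**Inputs** (Table 2, asymptomatic grade 2 row): limits SBP < 140 mmHg and DBP < 90 mmHg, joined by *or*.

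**Rules compared**
- Printed: controlled if SBP < 140 or DBP < 90. Its complement is SBP ≥ 140 and DBP ≥ 90, so control fails only when both pressures are raised.
- Corrected: controlled if SBP < 140 and DBP < 90. Its complement is SBP ≥ 140 or DBP ≥ 90, so control fails when either is raised.

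| Reading (mmHg) | SBP < 140 | DBP < 90 | Printed (*or*) | Corrected (*and*) |
|---|---|---|---|---|
| 135/85 | yes | yes | controlled | controlled |
| 139/89 | yes | yes | controlled | controlled |
| 155/85 | no | yes | controlled | not controlled |
| 135/95 | yes | no | controlled | not controlled |
| 175/85 | no | yes | controlled | not controlled |
| 135/105 | yes | no | controlled | not controlled |
| 140/90 | no | no | not controlled | not controlled |
| 155/95 | no | no | not controlled | not controlled |

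The two rules differ exactly where one pressure is raised and the other is not. Taken by itself, the printed definition then accepts the reading however high the raised pressure is.

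**Comparison with the first hypertension row.** Its ranges end at 139 and 89, so the control limits of 140 and 90 begin where the monitoring ranges stop. That suggests 140 and 90 were meant as a limit for each pressure separately. In 155/85 the systolic value of 155 is above its range, and in 135/95 the diastolic value of 95 is above its range. The other value of each pair lies inside its range.

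**The case against.** The strongest reply is that the word changes no compulsory dosing action in its own row. Anlotinib continues at the initial dose while control is sought, and a failure to reach control only permits a reduction at the investigator's discretion. The dose column repeats that discretion without a condition. Nothing in the row forbids further antihypertensive adjustment once the printed end point is met. All of this stands, and it limits the consequence.

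It can also be said that the rows apply by CTCAE grade. A patient who still meets asymptomatic grade 2 is still in a row that calls for antihypertensive treatment, and one who reaches grade 3 moves to the row that stops anlotinib. This stands in part. Grading may catch a high single pressure, but the article prints no blood pressure limits for the grades, so the size of the remaining gap cannot be fixed from it. A patient could also stay in a grade row while the printed definition calls the pressure controlled.

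Most clinicians may read *and* regardless. That is a reason to expect little harm, not a reason to leave the threshold as it is.

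Four stronger inferences are not supported:

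- *That anlotinib may restart after grade 3 hypertension with one pressure still raised.* The restart row gives no numbers and does not refer back to the row above. Carry-over is plausible but not stated.
- *That a systolic pressure of any height is accepted under the table.* This is true of the definition in isolation, not of a table that works by grade.
- *That 155/85 and 135/95 lie outside the monitoring row altogether.* That row is also joined by *or*, so 155/85 meets it through the diastolic 85 and 135/95 through the systolic 135. Only the raised component lies above its range.
- *That exclusion 11 ("systolic blood pressure ≥ 160 mmHg and diastolic blood pressure ≥ 100 mmHg") ought to catch these readings and fails to.* It is an entry criterion and could not serve as an on-treatment check.

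**Conclusion.** The point holds as an error in a stated safety threshold. As printed, a reading with exactly one raised pressure, such as 155/85 or 135/95, satisfies the end point for antihypertensive adjustment and does not trigger the two-week condition for a possible dose reduction.

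The size is modest. The definition is certain to misclassify such readings, but the number of patients who would show them cannot be derived from the article. Its effect is confined to how long antihypertensives are adjusted and whether a discretionary reduction is prompted. The objective response rate and the sample size do not depend on it.

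The conclusion rests on two things: that the row is read as worded, and that control is meant to require both pressures below their limits, as the adjoining monitoring ranges suggest.

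**What to change.** In the asymptomatic grade 2 row of Table 2, define effective control as SBP < 140 mmHg **and** DBP < 90 mmHg. Preferably add that the same definition applies to the term in the symptomatic grade 2 or grade 3 row, so that restart has a stated threshold.

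This is one word and one cross-reference, by amendment or a clarification letter to sites. The downside is slightly more antihypertensive adjustment or dose reduction and, if the definition also governs restart, possibly longer anlotinib holds.

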**Fluozopalib**			
**Grade 3 hematological toxicity**	**Grade 3 leukopenia not accompanied by fever**	**Discontinue fluozopalib till Grade ≤ 2 hematological toxicity, then fluozopalib was continued at an initial dose level**	**150 mg twice daily**
		**While grade 3 hematologic toxicity occurred again, discontinue fluozopalib till grade ≤ 2 hematological toxicity, then fluozopalib was continued at a lower dose level**	**100 mg twice daily**
		**While grade 3 hematologic toxicity occurred third time, discontinue fluozopalib till grade ≤ 2 hematological toxicity, then fluozopalib was continued at a much lower dose level**	**50 mg twice daily**
	**Grade 3 neutropenia not accompanied by fever**	**Discontinue fluozopalib till Grade ≤ 2 hematological toxicity, then fluozopalib was continued at an initial dose level**	**150 mg twice daily**
		**While grade 3 hematologic toxicity occurred again, discontinue fluozopalib till grade ≤ 2 hematological toxicity, then fluozopalib was continued at a lower dose level**	**100 mg twice daily**
		**While grade 3 hematologic toxicity occurred third time, discontinue fluozopalib till grade ≤ 2 hematological toxicity, then fluozopalib was continued at a much lower dose level**	**50 mg twice daily**
	**Grade 3 neutropenia accompanied by fever**	**Discontinue fluozopalib till Grade ≤ 2 hematological toxicity, then fluozopalib was continued at a lower dose level**	**100 mg twice daily**
		**While occurred again, discontinue fluozopalib till grade ≤ 2 hematological toxicity, then fluozopalib was continued at a much lower dose level**	**50 mg twice daily**
	**Grade 3 leukopenia or neutropenia accompanied by grade 2 thrombocytopenia/grade 2 anemia**	**Discontinue fluozopalib till Grade ≤ 2 hematological toxicity, then fluozopalib was continued at a lower dose level**	**100 mg twice daily**
		**While occurred again, discontinue fluozopalib till grade ≤ 2 hematological toxicity, then fluozopalib was continued at a much lower dose level**	**50 mg twice daily**
**Grade 4 hematological toxicity**		**Discontinue fluozopalib till Grade ≤ 2 hematological toxicity, then fluozopalib was continued at a lower dose level**	**100 mg twice daily**
		**While occurred again, discontinue fluozopalib till grade ≤ 2 hematological toxicity, then fluozopalib was continued at a much lower dose level**	**50 mg twice daily**
**Grade 3 non-hematologic toxicity**		**Discontinue fluozopalib till Grade ≤ 1 hematological toxicity, then fluozopalib was continued at an initial dose level or a lower dose level**	**150 mg twice daily or 100 mg twice daily**
		**While occurred again, discontinue fluozopalib till grade ≤ 1 hematological toxicity, then fluozopalib was continued at a lower dose level**	**100 mg twice daily or 50 mg twice daily**
**Grade 4 non-hematologic toxicity**		**Discontinue fluozopalib till Grade ≤ 1 hematological toxicity, then fluozopalib was continued at a lower dose level**	**100 mg twice daily**
		**While occurred again, discontinue fluozopalib till grade ≤ 1 hematological toxicity, then fluozopalib was continued at a much lower dose level or discontinue**	**50 mg twice daily or discontinue**

*NCI CTCAE* National Cancer Institute Common Terminology Criteria for Adverse Events, *SBP* Systolic blood pressure, *DBP* Diastolic blood pressure

Take 1 capsule (8 mg) of anlotinib once daily on an empty stomach before breakfast. Stop 1 week after 2 consecutive weeks of oral administration, i.e. 3 weeks (21 days) as a treatment cycle. In case of missed dose, no additional dose will be given if the time for the next dose is confirmed to be shorter than 12 h. Patients with disease control (CR + PR + SD) and tolerable adverse effects will continue the dose.

For oral fluzoparib, it should be swallowed whole either after a meal or on an empty stomach (recommended after a meal). Take 3 capsules (150 mg) twice daily for 14 days, and 7 days of discontinuation as a treatment cycle (21 days). In case of a missed dose, the next dose should be taken normally at the scheduled time.

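### Table 2 names only grade 2 companion cytopenias for the 100 mg fluzoparib restart, so as printed a first afebrile event with a grade 3 companion restarts at full dose

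*Protocol article*

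**What the plan says.** The fluzoparib part of Table 2 has a block for grade 3 haematological toxicity with four triggers. They are numbered here in printed order; the table does not number them.

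- Row 1: "Grade 3 leukopenia not accompanied by fever".
- Row 2: "Grade 3 neutropenia not accompanied by fever".
- Row 3: "Grade 3 neutropenia accompanied by fever".
- Row 4: "Grade 3 leukopenia or neutropenia accompanied by grade 2 thrombocytopenia/grade 2 anemia".

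For a first event, rows 1 and 2 say "Discontinue fluozopalib till Grade ≤ 2 hematological toxicity, then fluozopalib was continued at an initial dose level", with 150 mg twice daily in the dose column. A later event in these rows lowers the dose: "While grade 3 hematologic toxicity occurred again, discontinue fluozopalib till grade ≤ 2 hematological toxicity", then 100 mg, and 50 mg at the third event. Rows 3 and 4 go to 100 mg at the first event and to 50 mg at the second. A separate row for grade 4 haematological toxicity also goes to 100 mg and then 50 mg. Neither the table nor the text below it says which row applies when two are met.

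**The concern.** Row 4 asks for a lower dose when a second cell line is affected, but it names that companion as grade 2, with no sign for a minimum. Rows 1 and 2 look only at white cells and fever. A patient whose platelets or haemoglobin have fallen further, to grade 3, can therefore miss row 4 and be left with the full-dose rows.

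This is a printed dosing rule that sites would follow. The Background says that anlotinib may in theory raise fluzoparib blood levels, so the restart dose after marrow toxicity matters. Changes of dose because of adverse events are also a listed safety endpoint. Centres that resolve the overlap differently could record the same event differently.

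**Working it through.** The plan gives no figure of its own on this point. The check is a literal matching of cases to rows, followed by dose arithmetic.

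**Inputs.** Triggers and doses are from Table 2. The schedule, 14 dosing days in a 21-day cycle, is from the dosing text below Table 2. The slash in row 4 is read as *or*.

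**Step 1: match the cases.** Take a first afebrile grade 3 leukopenia or neutropenia with no grade 4 cytopenia. Rows 1 and/or 2 always match (150 mg). Row 3 never matches, because there is no fever. Row 4 matches (100 mg) only if platelets or haemoglobin are exactly grade 2.

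| Platelets | Hb grade ≤ 1 | Hb grade 2 | Hb grade 3 |
|---|---|---|---|
| grade ≤ 1 | 150 | 150 and 100 | **150** |
| grade 2 | 150 and 100 | 150 and 100 | 150 and 100 |
| grade 3 | **150** | 150 and 100 | **150** |

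Of the 9 cells, 3 have a grade 3 companion and match 150 mg only (bold), 5 match two doses, and 1 (no companion above grade 1) is 150 mg as intended. Where one companion is grade 3 and the other exactly grade 2, row 4 is met, so those cells are not part of the claim.

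**Step 2: dose per cycle.**

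- 150 mg: 150 × 2 × 14 = 4,200 mg
- 100 mg: 100 × 2 × 14 = 2,800 mg
- 50 mg: 50 × 2 × 14 = 1,400 mg

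The first-event gap is 4,200 against 2,800 mg, and 1 − 2,800/4,200 = 33%. If row 4 overrides and the same picture recurs, the second-event doses are 2,800 mg (rows 1 and 2) against 1,400 mg (row 4).

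**Step 3: compare a grade 3 companion with a grade 2 companion under each reading.**

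| Reading | Grade 3 companion | Grade 2 companion |
|---|---|---|
| Row 4 overrides, grade 2 taken literally | 150 | 100 |
| No precedence, grade 2 taken literally | 150 | 150 or 100 |
| Rows 1 and 2 prevail | 150 | 150 |
| Row 4 overrides, grade 2 taken as a minimum | 100 | 100 |

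The third reading almost empties row 4. It would change no afebrile dose, and febrile neutropenia already goes to 100 mg under row 3, so only febrile leukopenia without neutropenia would be left. An override is therefore the likely intention. The fourth reading is clinically sensible but is not what is printed. Table 2 does use inequality signs elsewhere: ≥ in the anlotinib bleeding row, and ≤ in row 4's own recovery condition.

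**Step 4: other rules that might rescue the case.** The hold until grade ≤ 2 does not set the restart dose. The step for a toxicity that occurs again concerns a later event, not a second cytopenia present at the first one. The grade 4 row needs a grade 4 toxicity. None of these changes the first restart dose.

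**The case against.** The strongest reply is that nobody would apply the table this way. Row 4 exists because a second lineage is involved, and a clinician would take a grade 3 companion to qualify all the more. If purpose is allowed to settle precedence, it should settle the grade as well, and both cases then get 100 mg. This stands as a guess at what was meant, and a missing ≥ sign is the likeliest explanation. It does not correct the printed row. Even with the sign added, rows 1 and 2 would still match the same patients at 150 mg.

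A reader might go further and infer that the table sets doses inversely to severity. The documents do not support that as a flat statement. It needs row 4 to override, which is not printed, together with a strictly literal grade 2. Two of the four readings give equal doses. Equal doses are no defect in themselves, since a first grade 4 toxicity also restarts at 100 mg.

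The article condenses a fuller protocol that is not shown, and precedence could be stated there. That weakens the complaint about missing precedence. It does not touch the grade wording, because the dose table is printed and the Intervention text refers to it for dose adjustment.

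The harm is also bounded. Restart waits for recovery to grade ≤ 2, and any later grade 3 event in rows 1 and 2 forces a reduction. The Background also concludes that the fluzoparib dose should be lowered, and it expects no rise in grade ≥ 3 events. All of this stands, and it limits how serious the point is.

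**Conclusion.** Wrong as written, with a narrow scope. For a first afebrile grade 3 leukopenia or neutropenia with a grade 3 companion, neither companion exactly grade 2 and none grade 4, the only matching rows restart fluzoparib at 150 mg twice daily. No reduction is prescribed. With a grade 2 companion, two doses match and the table does not choose between them. If row 4 is meant to override, the worse two-lineage toxicity restarts at 4,200 mg per cycle against 2,800 mg for the milder one. That size depends on the override, which is likely but inferred.

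A reader might want a frequency from the Background rates of grade ≥ 3 anaemia (25.1%), low platelets (16.8%) and low neutrophils (12.6%). They do not give one. They are separate rates from another study, they include grade 4 events, they say nothing about which events coincide or about fever, and no leukopenia rate is given. How often the case arises in this trial is unknown. No effect on the objective response rate is claimed. The point should be corrected as a dosing-safety rule.

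**What to change.** In row 4, replace each *grade 2* with *grade ≥ 2* and the slash with *and/or*. To rows 1 and 2 add *and without grade ≥ 2 thrombocytopenia or anemia*. State that any grade 4 cytopenia follows the grade 4 row. Both changes are needed, because the ≥ sign alone leaves the overlap with rows 1 and 2. In the nine-cell grid, 8 cells then give 100 mg, 1 gives 150 mg, and none gives two doses.

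Two neighbouring cases would still match no row and need lines of their own, with doses set by the sponsor. They are a first febrile grade 3 leukopenia without neutropenia (companions ≤ grade 1) and a first isolated grade 3 anaemia or thrombocytopenia. Candidates are row 3's steps (100, then 50 mg) for the former and the steps of rows 1 and 2 (150, 100, then 50 mg) for the latter.

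The cost is a wording change, made by a minor amendment or a notice to sites. The downside is slightly more dose reductions: in the 3 cells with a grade 3 companion, and in the 5 dual-match cells wherever a centre now uses 150 mg. No extra patients or procedures are needed.

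### Table 2 lets fluzoparib restart after grade 3–4 non-haematological toxicity on the strength of haematological recovery, in all four instructions

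*Protocol article*

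**What the plan says.** Table 2 (Intervention section) sets the dose-adjustment rules. Under fluzoparib, two rows are labelled "Grade 3 non-hematologic toxicity" and "Grade 4 non-hematologic toxicity". Each has one instruction for a first event and one for a repeat.

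- Grade 3, first event: hold until grade ≤ 1 "hematological toxicity, then fluozopalib was continued at an initial dose level or a lower dose level".
- Grade 4, repeat event: hold until grade ≤ 1 "hematological toxicity, then fluozopalib was continued at a much lower dose level or discontinue".
- The other two instructions (grade 3 repeat, grade 4 first) carry the same grade ≤ 1 haematological condition.

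The haematological rows above them, including the one labelled "Grade 4 hematological toxicity", all restart at haematological grade ≤ 2. In the anlotinib part of the table, the grade 2 bleeding and coagulation row ties restart to the event itself: "Discontinue anlotinib, till AE" ≤ 1.

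On blood pressure, exclusion criterion 11 in Table 1 reads "Patients with poor blood pressure control (systolic blood pressure" ≥ 160 mmHg *and* diastolic ≥ 100 mmHg), after drug therapy. The Table 2 row for asymptomatic grade 2 hypertension says "Start taking antihypertension medication or adjust its dose till blood pressure is effectively controlled", and defines control as systolic < 140 mmHg *or* diastolic < 90 mmHg.

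**The concern.** A restart rule should require recovery of the toxicity that stopped the drug. Here the trigger is non-haematological and the release condition is haematological, so the two are unconnected. The rule can fail in both directions: it can release the drug while a severe event is still present, or withhold it because of a blood count that had nothing to do with the interruption.

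What is at stake is patient safety and the timing of restart. The Background section gives two reasons why these rows may well be needed. It lists anlotinib's grade 3 or higher reactions as mainly hypertension, hand-foot skin reaction and proteinuria, all non-haematological. It also says that anlotinib may raise fluzoparib exposure, and that no clinical study of the pair had been reported or registered. The Endpoints section counts the proportion of patients with dose adjustment due to adverse events among the safety endpoints, and that figure could be affected if centres read the rule differently.

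**Working it through.** No sample size, power or event figure is involved. The check compares each row label with the recovery condition in its own cell, and then asks what the printed rule does to particular patients.

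**Fluzoparib instructions in Table 2**

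| Trigger | Instructions | Restart condition printed | Matches trigger? |
|---|---|---|---|
| Grade 3 leukopenia, no fever | 3 | haematological grade ≤ 2 | yes |
| Grade 3 neutropenia, no fever | 3 | haematological grade ≤ 2 | yes |
| Grade 3 neutropenia with fever | 2 | haematological grade ≤ 2 | yes |
| Grade 3 leukopenia or neutropenia with grade 2 thrombocytopenia or anaemia | 2 | haematological grade ≤ 2 | yes |
| Grade 4 haematological | 2 | haematological grade ≤ 2 | yes |
| Grade 3 non-haematological | 2 | haematological grade ≤ 1 | **no** |
| Grade 4 non-haematological | 2 | haematological grade ≤ 1 | **no** |

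Haematological instructions: 3 + 3 + 2 + 2 + 2 = 12, all consistent with their trigger. Non-haematological instructions: 2 + 2 = 4, none consistent. No other part of the article gives a restart rule for non-haematological events.

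**What the printed rule does**

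1. *Normal counts, grade 3 non-haematological event persisting.* Haematological grade ≤ 1 is already met. Restart is allowed at 150 or 100 mg twice daily (first event), or at 100 or 50 mg (repeat).
2. *Normal counts, grade 4 non-haematological event persisting.* The condition is again already met. Restart is allowed at 100 mg twice daily (first event), or at 50 mg with discontinuation as the alternative (repeat).
3. *Event fully resolved, grade 2 blood count.* Haematological grade ≤ 1 is not met, so fluzoparib stays on hold. A patient recovering from grade 4 haematological toxicity with the same grade 2 count may restart.

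Case 3 shows that the printed wording cannot be what was meant. It would demand better counts after a non-haematological event than after the most severe haematological toxicity in the table.

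**What was meant.** The threshold moves from ≤ 2 to ≤ 1 exactly where the row labels change from haematological to non-haematological, and the anlotinib bleeding row uses ≤ 1 for the event itself. Both point to a dropped *non-*. The row labels keep the prefix, so this is not a text-extraction effect.

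**Secondary point: blood pressure.** Take 170/85 mmHg.

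- Exclusion 11 as printed: (170 ≥ 160) *and* (85 ≥ 100) = true and false = false, so not excluded. With *or*: true, excluded.
- Control target as printed: (170 < 140) *or* (85 < 90) = false or true = true, so controlled. With *and*: false, not controlled.

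**The case against.** The best case on the other side is that this is an evident slip with a recoverable meaning. For a patient with normal counts the hold would end as soon as it began, which pushes any reader towards the intended rule. The table's management column presupposes active treatment and observation, dosing ends at intolerable toxicity, and the investigator may stop treatment for other reasons. A restart during a persisting grade 4 event is therefore unlikely. That is fair as a statement about likelihood, but none of these provisions sets a recovery grade for restart. The sentence on continuing when side effects are tolerable sits in the anlotinib paragraph and sets none either. As written, the unsafe restart complies with the rule and the sensible delay departs from it.

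A second objection is that the article condenses a protocol that is not shown, so the slip may have arisen only in the article. That cannot be ruled out, and it bears on how the correction is made. It does not excuse a rule that the article prints in detail and prints wrongly.

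On blood pressure, three limits stand. The numeric target appears only in the asymptomatic grade 2 row. A patient missed by criterion 11 could still be excluded under the general safety criterion 21. And enrolment was estimated to finish in May 2022, before the article appeared in August 2023. These make the point secondary, but both connectors are still wrong as printed.

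**Conclusion.** The concern holds: the restart rule is wrong as written in 4 of 4 non-haematological instructions, and nothing elsewhere in the article corrects it. The worst literal consequence is a restart at the full 150 mg twice daily with an unresolved grade 3 event. How many patients this would touch cannot be stated, because the article gives no rate of grade ≥ 3 non-haematological events for the combination.

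The conclusion assumes only that the table is applied as printed. That the prefix was dropped by accident is an inference from the table's structure, though a strong one. The sample size and the objective response rate analysis are unaffected. The blood-pressure connectors are a separate, lesser error of the same kind.

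**What to change.** In the four non-haematological fluzoparib cells of Table 2, replace the haematological condition with one tied to the event: hold fluzoparib until the non-haematological toxicity that caused the interruption has recovered to grade ≤ 1, then resume at the level already printed. Keep the grade and dose levels as they are.

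In the same amendment, define blood-pressure control in Table 2 as systolic < 140 mmHg *and* diastolic < 90 mmHg, and word exclusion 11 as systolic ≥ 160 mmHg *or* diastolic ≥ 100 mmHg.

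Check the full protocol held at the sites for the same wording, amend it where it is present, send sites a short memo, and correct the article in any case.

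The cost is wording in four cells, two connectors and the memo. Sample size, endpoints and data collection do not change. The exclusion 11 change is slightly stricter and matters only while enrolment is open. The Table 2 changes apply to every patient still on treatment.
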